**Sexual concurrency**

We will assess concurrency during the two most recent sexual partnerships using the direct method. Participants are asked if they had sex with anyone else while in a sexual partnership with either of their two most recent partners. In our previous work in Tanzania, we found that the direct method was concordant with the UNAIDS calendar method at least 82% of the time([Eaton, 2009](#_ENREF_23)). We will ask participants how many sexual relationships they had at the same time during the past 6 months.

Concurrency in the last 12 months will also be assessed using an indirect method. Participants will be asked to list nicknames for their three longest sexual relationships in the past 12 months. For each partner mentioned participants will answer how recently they last had sex with each partner, when they first had sex with each partner, and if they are still having sex with each partner.

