## 3.3 Study Duration and Endpoints

The intervention will be implemented for two years, and the total duration of the trial will be 5 years. **The primary endpoints** are sexually transmitted infections including Neisseria gonorrhea (NG), Trichomonas vaginalis (TV), Chlamydia trachomatis (CT), and perpetration of physical or sexual violence against a sexual partner. A random sample of 50% of participating men will be flagged for an STI test at baseline to assess relative prevalence, and all men will be tested at endline. A test of relative prevalence at baseline will aid in establishing equivalency in the two arms; any lack of equivalency then will be controlled for appropriately at endline. All participants will complete a behavioral assessment at baseline, 12 months and 30 months to assess secondary objectives. **Secondary endpoints** are HIV risk and protective behaviors including: gender equity, alcohol and drug use, sexual relations and risk behavior, uptake of HIV counseling and testing; unprotected sexual intercourse; consistent condom use; delay of sexual debut; number of sexual partners, and sexual concurrency. **Key mediators** are hope, future orientation, social cohesion, collective efficacy, emotional distress, sexual networks, social support and social influence.

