## 7.4 Secondary Outcomes - Behavioral Outcomes

All secondary outcomes except for microfinance outcomes will be measured at baseline, 12 months and 30 months. Microfinance outcomes will be measured at 12 and 30 months only.

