| Q1509 | | Are you still having sex with PARTNER 1? | NO  YES | 0  1 | |  | SEXCUR_P1 |
| Q1510 | | How often do/did you have sex with PARTNER 1? | EVERY DAY  A FEW TIMES A WEEK  FEW TIMES A MONTH  ABOUT ONCE A MONTH  ONLY 1-2 TIMES EVER | 1  2  3  4  5 | |  | SEXFRQ_P1 |
| Q1511 | | During the last (most recent) time you had sex with this partner, did you use a condom? | NO  YES  DON’T KNOW | 0  1  88 | |  | CNDUSE_P1 |
| Q1512 | | How many times would you say you had sex with PARTNER 1 during the last one month you had sex with him/her? | _____________ |  | |  | NUMSEX_P1 |
| Q1513 | | Of these (Response from Q1512) times, how many times would you say you used a condom? | _____________ |  | |  | NUMCND_P1 |
| Q1514 | | Did you ever give PARTNER 1 money in exchange for having sex with you? | NO  YES | 0  1 | |  | GIVFSP_P1 |
| Q1515 | | Did PARTNER 1 ever give YOU money in exchange for having sex? | NO  YES | 0  1 | |  | RECFSP_P1 |
| Q1516 | | Did you use a condom the last time money was given or exchanged for sex with PARTNER 1? | NO  YES | 0  1 | | **ASK ONLY IF either Q1514 or Q1515 =1** | CNDM_P1 |
| Q1517 | | The last time you had sex with PARTNER 1, did you drink alcohol before or during sex? | NO  YES | 0  1 | |  | DRNK1_P1 |
| Q1518 | | The last time you had sex with PARTNER 1, did PARTNER 1 drink alcohol before or during sex with you? | NO  YES  DON’T KNOW | 0  1  88 | |  | DRINK2_P1 |
| Q1519 | | While you were in a sexual relationship with PARTNER 1, did you have sex with anybody else? | NO  YES | 0  1 | |  | SXCUR_P1 |
| Q1520 | | As far as you know, during the time you were having a sexual relationship with PARTNER 1, do you think PARTNER 1 had sex with other people? | NO  YES | 0  1 | |  | MCP_P1 |
| Q1521 | | How confident are you that you can use a condom with PARTNER 1? | VERY CONFIDENT  SOMEWHAT CONFIDENT  NOT AT ALL CONFIDENT | 1  2  3 | |  | UCND_P1 |
| Q1522 | | How confident are you that you can discuss HIV with PARTNER 1? | VERY CONFIDENT  SOMEWHAT CONFIDENT  NOT AT ALL CONFIDENT | 1  2  3 | |  | TLKHIV_P1 |
| Q1523 | | Have you ever discussed getting an HIV test with PARTNER 1? | NO  YES | 0  1 | |  | TLKTST_P1 |
| Q1524 | | Have you ever gone together with PARTNER 1 for an HIV test? | NO  YES | 0  1 | |  | TOGTST_P1 |
| Q1525 | | Has PARTNER 1 shared the results of their HIV test in the past 12 months? | NO  YES | 0  1 | |  | TSTDISC_P1 |

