| Q1526 | | In the past 12 months, has PARTNER 1 ever hit, slapped, kicked, pushed, shoved or otherwise physically hurt you? | NO  YES | 0  1 | |  | VICVIO_P1 |
| Q1527 | | In the past 12 months, have you ever hit, slapped, kicked, pushed, shoved or otherwise physically hurt PARTNER 1? | NO  YES | 0  1 | |  | PERVIO_P1 |
| PARTNER #2  *Interviewer:*  **→** Now lets talk about your other most recent partners (excluding the partner we just talked about). | | | | | | | |
| Q1528 | | Tell me about the person you had sex with most recently within the last 12 months who is not PARTNER 1. What is the nickname or initials I could use to talk about this person? | PARTNER #2 | |  |  | NAME_P2 |
| Q1529 | | When was the most recent time you had sex with PARTNER 2? | MONTHS __ __  WEEKS __ __  DAYS __ __ | |  |  | RECSEX_P2 |
| Q1530 | | Is PARTNER 2 a man or a woman? | MAN  WOMAN | | 1  2 |  | GEND_P2 |
| Q1531 | | Where did you meet PARTNER 2? | HOME  SCHOOL  WORK  MY CAMP  ANOTHER CAMP  MOSQUE/CHURCH  STREET  CLUB/BAR  GUEST HOUSE  BEACH  PARTY  WEDDING/FUNERAL  OTHER___________________ | | 1  2  3  4  5  6  7  8  9  10  11  12  13 |  | MEET_P2  METP1_S |
| Q1532 | | How long have you been having sex with this partner? | YEARS_________________  MONTHS_______________  WEEKS_________________ | |  |  | SEXDY_P2  SEXDM_P2  SEXDW_P2 |
| Q1533 | | What type of relationship do you have with PARTNER 2? | SPOUSE  POLYGAMOUS SPOUSE  COHABITING PARTNER  GIRLFRIEND/BOYFRIEND  FRIEND  CASUAL ACQUAINTANCE  COMMERCIAL SEX WORKER  ONE TIME PARTNER  OTHER___________________ | | 1  2  3  4  5  6  7  8  9 |  | RELP_P2  RELP_P2_S |
| Q1534 | | (If needed: To the best of your knowledge) How old is _____ PARTNER 2)? | __ __ YEARS | |  |  | AGE_P2 |
| Q1535 | | Is PARTNER 2 a member of this camp? | NO  YES  DON’T KNOW | | 0  1  88 |  | CAMPM_P2 |
| Q1536 | | Are you still having sex with PARTNER 2? | NO  YES | | 0  1 |  | SEXCUR_P2 |
| Q1537 | | How often do/did you have sex with PARTNER 2? | EVERY DAY  A FEW TIMES A WEEK  FEW TIMES A MONTH  ABOUT ONCE A MONTH  ONLY 1-2 TIMES EVER | | 1  2  3  4  5 |  | SEXFRQ_P2 |
| Q1538 | | During the last (most recent) time you had sex with this partner, did you use a condom? | NO  YES  DON’T KNOW | | 0  1  88 |  | CNDUSE_P2 |
| Q1539 | | How many times would you say you had sex with PARTNER 2 during the last one month you had sex with him/her? | _____________ | |  |  | NUMSEX_P2 |

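### Section 7.4.1 promises a six-month concurrency question that the Appendix D survey does not contain, and the direct concurrency items have no look-back period

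*Protocol*

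**What the plan says.** Section 3.3 closes its list of secondary endpoints with "number of sexual partners, and sexual concurrency". Section 7.4 adds: "All secondary outcomes except for microfinance outcomes will be measured at baseline, 12 months and 30 months". Section 8.2.3 (Behavioral Survey) says that the survey form serves at baseline and at both follow-ups.

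Section 7.4.1 (Sexual concurrency) describes three measures:

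- A direct method: "We will assess concurrency during the two most recent sexual partnerships using the direct method". It continues: "Participants are asked if they had sex with anyone else while in a sexual partnership with either of their two most recent partners".
- A six-month count: "We will ask participants how many sexual relationships they had at the same time during the past 6 months".
- An indirect method: "Concurrency in the last 12 months will also be assessed using an indirect method". This is built from the timing of a man's three longest relationships in that period. The Sexual Network paragraph of the same section also selects partners by longest relationship, up to three.

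Appendix D, Section 15, works differently. Partner 1 is the longest relationship among partners of the last 12 months. Partner 2 is chosen by "Tell me about the person you had sex with most recently within the last 12 months who is not PARTNER 1". Partner 3 is the next most recent before Partner 2. The direct item for Partner 1 (Q1519) reads "While you were in a sexual relationship with PARTNER 1, did you have sex with anybody else", and Q1546 and Q1573 repeat it for Partners 2 and 3.

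**The concern.** A promised component of a named secondary endpoint has no question behind it. Of the measures that remain, the direct item covers the whole life of each relationship. A man who stops having other partners after enrolment but keeps the same main partner will still truthfully answer yes at 12 and 30 months. The intervention cannot change that answer, so the item responds less to a real effect than a time-limited one would. The text and the form also disagree on which partners are asked about, so the indirect measure would not be computed on the partners the protocol names.

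**Working it through.** No figure in the protocol rests on this point, so the check sets Section 7.4.1 against Appendix D item by item.

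**1. Six-month count.** Sections 14 and 15 (Q1401 to Q1414, Q1501 to Q1581) hold three counts of the man's own partners: lifetime (Q1405), past 12 months (Q1406), and the split of Q1406 by sex (Q1407). None asks about simultaneous partners. Elsewhere, multiple partnerships come up only as friends' behaviour (Section 12) and as an attitude (Q1302). Items asking for simultaneous relationships in the past six months: 0.

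**2. Direct method, partners covered.** If Partner 1 is among the man's two most recent partners of the past 12 months, those two are Partners 1 and 2. If not, they are Partners 2 and 3. Either way both are covered. Q1502, Q1529 and Q1556 give the recency needed to identify them, and all three partners carry the direct question.

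**3. Direct method, period covered.** Items with a look-back: 0 of 3. Let D be the length of the relationship in months, and assume visits are timed from the start of the intervention.

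- At 12 months, D − 12 months of the relationship precede the intervention whenever D > 12.
- At 30 months, D − 30 months precede it whenever D > 30.

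Partner 1 is by construction the longest relationship, and Q1505 accepts a length in years. The partner-specific violence items in the same section (Q1526, Q1527) are limited to 12 months, so a limit is workable in this format.

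**4. Indirect method.** The form records time since last sex (L), duration (D) and whether the relationship continues, for up to three partners: Q1502/Q1505/Q1509, Q1529/Q1532/Q1536 and Q1556/Q1559/Q1563. Section 7.4.1 asks for the date of first sex; approximately, the start lies S = L + D months ago, with L taken as 0 for a current partner. Partners i and j overlap within the last W months if min(S_i, S_j, W) > max(L_i, L_j). With W = 12 this gives the indirect measure. With W = 6 it approximates six-month overlap among the partners listed.

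**5. Indirect method, partners covered.** The form takes the longest partner plus the next most recent; the text takes the three longest. For a man with at most three partners in the past 12 months the sets coincide. With more than three they need not. Q1555 states no 12-month limit for Partner 3, but Q1556 lets an older partner be dropped.

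**6. Where each window falls**, on the timing assumption in step 3.

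- Six-month window: it opens at 12 − 6 = 6 and 30 − 6 = 24 months, after the start at both visits.
- Twelve-month window: it opens at 12 − 12 = 0 and 30 − 12 = 18 months, so at the first follow-up it has no margin.

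**The case against.** The strongest reply is that little is lost. The direct method can be carried out as written. Section 7.4.1 gives it no look-back, so the form follows the text on that point. The 12-month indirect measure supplies a time-bounded outcome. All of this stands, and it rules out a reading that someone comparing text and form might reach: that concurrency cannot be measured, or that the endpoint as a whole is a lifetime-of-relationship measure. One of three components is missing, and one of the other two lacks a time limit.

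A second reply is that Appendix D is probably the baseline form. Section 6.3 cites it for the baseline survey, it opens with enrolment screening, and it lacks other measures described in Section 7, such as moral agency, which is set for midpoint and endpoint only. A follow-up form could therefore contain the question. This limits what can be said about follow-up, but it does not remove the discrepancy: concurrency, unlike moral agency, is required at every wave, and Section 8.2.3 has the form used at all of them.

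Third, rewording the direct items would break comparability with baseline answers and depart from the method for which Section 7.4.1 reports at least 82% concordance with the calendar method. That is a sound reason to leave them alone. Which measure becomes the analysed endpoint may also be settled in a statistical analysis plan that is not shown; the mismatch between text and form lies in the protocol itself.

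**Conclusion.** The point holds as a discrepancy between protocol and survey, plus a weakness in one item, affecting one secondary endpoint and neither primary endpoint. The six-month question is promised and absent. The direct items can carry pre-intervention behaviour into both follow-ups when relationships are long. The indirect measure is largely recoverable but does not use the partners the text names.

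Under randomisation the carry-over should be similar by arm, so the expected consequence is dilution. If a fraction f of the yes answers expected without an effect refers wholly to the time before the intervention, a true relative reduction r appears as r × (1 − f). The documents give no value for f, which could lie anywhere between 0 and 1. A reader might assume a quarter to a half and conclude that a 30% reduction would show as 22.5% to 15% (0.30 × 0.75 = 0.225; 0.30 × 0.50 = 0.15), but nothing in the protocol supports that range. Newer relationships are unaffected.

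Nor should the 47% six-month concurrency in Section 1.7 be read as a planning figure. It is a descriptive prevalence among men in the preliminary study who had ever had sex, and the power calculation in Section 9.1.1 does not use concurrency.

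**What to change.** - Add the promised six-month question to the 12- and 30-month surveys. Use it, or the 12-month indirect measure, as the time-bounded concurrency outcome. The six-month item has the clearer window (step 6) and is not capped at three partners.
- Leave Q1519, Q1546 and Q1573 as they are, for comparability with baseline, and treat them as supportive.
- Reconcile the partner-selection wording in Section 7.4.1 (Sexual concurrency and Sexual Network) with Appendix D, Section 15. State how men with more than three partners are handled.

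The cost is one extra question per wave and a text correction. If the question was not asked at baseline there will be no baseline value to adjust for or compare, but the randomised arms can still be compared at each follow-up. If the question is not added, its sentence should come out of Section 7.4.1, and the indirect measure would be the only time-bounded outcome, with the three-partner cap stated.

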**Gender Equity**

We will use the Inequitible Gender Norms subscale of the Gender Equitable Men’s Scale (GEMS) validated by Shattuck et al. in Tanzania and Ghana ([Shattuck et al., 2013](#_ENREF_83)). The scale demonstrated good reliability in two populations of adult men in Tanzania (Cronbach’s a = .72 and .87). The scale was developed by Pulerwitz and Barker ([Julie Pulerwitz & Gary Barker, 2008](#_ENREF_71)), but the validated measure used in Tanzania and Ghana eliminates two questions that measured attitude towards homosexuality. Two other questions presented in the first person were changed to men in general to match all other questions. The scale asks participants do indicate how much they agree with scenarios describing roles and relations of men to women on a 4-point Likert scale from 1 = Strongly Agree to 4 = Strongly Disagree.

**Gender Role Conflict**

We will use 16 items from the Gender Role Conflict Scale (GRCS), developed and originally validated by O’Neil et al. in the United States to measure the impact of socialized gender roles on men (O’Neil et al., 1986). The scale initially demonstrated good internal consistency (Cronbach’s a = .75-.85). Since then, hundreds of studies have used the GRCS in the United States and globally and have assessed its validity and reliability. A recent review of over 200 studies confirmed good internal consistency (Cronbach’s a ranging from .70 to .89) and construct validity, with moderate factor intercorrelation (.35-.68). The review found the measure was positively correlated with depression, anxiety, stress, as well as measures of self-esteem, substance use, and shame (O’Neil, 2008; Wester et al., 2012).

**HIV Stigma**

We will incorporate three questions about camp-level perceptions of HIV from work in Uganda done by Singer and Charlebois ([Singer](#_ENREF_85)). These questions ask participants to answer how many camp members are likely to avoid people with HIV, if HIV is the result of wrong behaviors, and if people with HIV have brought shame on their families. Responses are on a 4-point Likert scale from 1 = No People to 4 = Most People.

**Alcohol and Drug Use**

Participants will be asked about lifetime use of alcohol and drugs. Participants who have used alcohol will be asked about use in the last month, frequency of use, frequency of use until intoxication, and if consumed greater than 5 drinks in one sitting. Participants who have used drugs will be asked about use and frequency of use in the last 12 months.

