**Behavioral Survey**

An approximately 1 hour behavioral survey instrument will be created and formatted in Samsung Galaxy tablets. The survey will be comprised of variables that assess, but are not limited to, demographic data, HIV risk and protective behaviors, social and sexual networks, gender-based violence perpetration and victimization, hope, collective efficacy, emotional distress, social support, alcohol and drug use, and work and expenditures. The behavioral survey form will be used at baseline, and 12 and 30 month follow-ups.

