***Interviewer:***

→ Now I’d like to ask you some questions about your drinking habits and substance use. I know that these are sensitive questions and want to remind you that your responses are confidential.

| **No.** | **Questions and Filters** | **Coding Categories** | **Codes** | **Skip to:** | **VARIABLE** |
| --- | --- | --- | --- | --- | --- |
| Q1001 | Have you ever used alcohol **in your lifetime?** | NO  YES | 0  1 | **Q1005** | ALC_EVR |
| Q1002 | **In the past month**, how often did you use any alcohol? If you don’t know exactly, give a best guess. | NEVER  LESS THAN ONCE A WEEK  1-3 TIMES A WEEK  >3 TIMES A WEEK | 0  1  2  3 | **Q1005** | ALC_FRQ |
| Q1003 | **In the past month**, how often, on average did you drink until you were intoxicated? If you don't know exactly give a best guess. | NEVER  LESS THAN ONCE A WEEK  1-3 TIMES A WEEK  >3 TIMES A WEEK | 0  1  2  3 | **Q1005** | DRNK_FRQ |
| Q1004 | **In the past month,** have you had 5 drinks or more during any one given occasion?  Probe: One drink equals one beer, one glass of wine, or one ounce of hard alcohol | NO  YES | 0  1 |  | ALC_BING |
| Q1005 | Have you ever used marijuana in your lifetime? | NO  YES | 0  1 | **Q1007** | MRJ_EVR |
| Q1006 | How often did you smoke marijuana in the last 12 months? | NOT AT ALL  EVERY DAY  A FEW TIMES A WEEK  ONCE OR TWICE A MONTH  ONCE EVERY FEW MONTHS | 0  1  2  3  4 |  | MRJ_FRQ |
| Q1007 | Have you ever smoked a “cocktail” (mixture of heroin and marijuana) in your lifetime? (I want to remind you that your response will be confidential) | NO  YES | 0  1 | **Q1009** | CKT_EVR |
| Q1008 | How often have you smoked “cocktails” in the last 12 months? | NOT AT ALL  EVERY DAY  A FEW TIMES A WEEK  ONCE OR TWICE A MONTH  ONCE EVERY FEW MONTHS | 0  1  2  3  4 |  | CKT_FRQ |
| Q1009 | Have you ever injected heroin, opium, or cocaine? | NO  YES | 0  1 |  | HINJ_EVR |

Section 11: Social Support

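### Injecting drug use is asked only as lifetime ever/never in the survey form shown, although Section 7.4.1 promises last-12-month use and frequency, so the item can show prevented initiation but not stopping or cutting down

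*Protocol*

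**What the plan says.** Section 3.3 of the Protocol lists the secondary endpoints, among them "gender equity, alcohol and drug use, sexual relations and risk behavior, uptake of HIV counseling and testing". Section 7.4 fixes their timing: "All secondary outcomes except for microfinance outcomes will be measured at baseline, 12 months and 30 months". The paragraph on alcohol and drug use in Section 7.4.1 describes the measure in two steps. First, "Participants will be asked about lifetime use of alcohol and drugs". Then, "Participants who have used drugs will be asked about use and frequency of use in the last 12 months". It makes no exception for injected drugs.

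Appendix D, Section 10, holds the drug items:

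- Marijuana: lifetime use (Q1005), then "How often did you smoke marijuana in the last 12 months" (Q1006).
- Smoked heroin-marijuana cocktail: lifetime use (Q1007), then frequency over the last 12 months (Q1008).
- Injecting: "Have you ever injected heroin, opium, or cocaine" (Q1009), answered no or yes. It is the last item of the section, and Section 11 on social support follows.

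Section 8.2.3 says of the survey: "The behavioral survey form will be used at baseline, and 12 and 30 month follow-ups". Section 9.1.3 plans between-arm odds ratios for behavioral outcomes at 12 and 30 months.

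**The concern.** The text promises a recent-use measure for every drug, and the instrument supplies it for two of three. The exception is injecting, which the protocol itself links to HIV: Section 4 supports the choice of wards partly with the share of syringes from male injectors that tested HIV positive.

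A lifetime item records history up to the interview. If it is reused at follow-up, a man who injected before baseline and has since stopped gives the same answer as one who still injects. The planned comparison would then miss one of the two ways the intervention could work on this behavior, and pre-baseline history would weaken the other. An analysis plan can choose among the items collected, but it cannot recover recent injecting that was never asked about.

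**Working it through.** **Text against instrument.** The plan states no figure for drug use, so there is none to reproduce.

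| Behavior | Lifetime item | Last-12-month frequency item | Matches Section 7.4.1 |
| --- | --- | --- | --- |
| Marijuana | Q1005 | Q1006 | yes |
| Smoked cocktail | Q1007 | Q1008 | yes |
| Injecting | Q1009 | none | no |

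No other item in Appendix D covers recent injecting. The nearest is the option in Q1631 on buying drugs in the past 30 days, which is not specific to injecting.

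**What a lifetime item can show.** Let E(t) = 1 if a man has injected at any time up to t. Then E(30) ≥ E(12) ≥ E(0) for every man who answers truthfully. Stopping leaves E at 1, and so does cutting down. Only starting changes E, from 0 to 1. Within the cohort, a fall could come only from inconsistent answers or from losing injectors to follow-up. Between arms, a difference can still arise if fewer intervention men start.

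**Illustration of the dilution.** The documents give no injecting rates. Assume a proportion e of 1% to 5% who had ever injected at baseline, a starting rate r of 0.2% to 1.0% per year, and 2.5 years of follow-up.

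Share of month-30 yes answers that predate the trial = e / [e + (1 − e)(1 − exp(−2.5r))]

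- e = 1%, r = 1.0%: 0.0100 / (0.0100 + 0.0244) = 0.29
- e = 3%, r = 0.5%: 0.0300 / (0.0300 + 0.0120) = 0.71
- e = 5%, r = 0.2%: 0.0500 / (0.0500 + 0.0047) = 0.91

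**Effect on the odds ratio.** Take e = 3% and r = 0.5%, and suppose the intervention halves the starting rate.

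- All men, control: 0.0300 + 0.97 × 0.01242 = 4.2%.
- All men, intervention: 0.0300 + 0.97 × 0.00623 = 3.6%.
- Odds ratio, all men: (0.0360/0.9640) / (0.0420/0.9580) = 0.85.
- Odds ratio among men answering no at baseline: (0.00623/0.99377) / (0.01242/0.98758) = 0.50.

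So under these assumptions a halving of initiation would appear as 0.85 in all men and as 0.50 in men who had never injected at baseline. If half of current injectors stopped, Q1009 would not change at all.

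**The case against.** **The follow-up form is not shown.** Section 6.3 cites Appendix D for the baseline survey, and its age check, with a 1998 birth year, fits a 2013 baseline. It has no section for moral agency, which Section 7.4.1 places at midpoint and endpoint, nor for the process questions that Sections 7.6.1 and 7.6.3 plan at those waves. The follow-up version must therefore differ somewhere. This stands as a limit: that Q1009 stays lifetime-only rests on the statement in Section 8.2.3 about reuse of the form. Nothing shown adds a recent-injecting item.

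**A stronger reading goes too far.** A reader might infer that this part of the drug-use endpoint can never improve after the intervention. The documents do not support that. Section 9.1.3 compares arms at follow-up, and prevented initiation would favor the intervention. Nor does any section name Q1009 as a component of the endpoint; Sections 2.3 and 3.3 say only alcohol and drug use. A last-12-month endpoint could already be built from Q1006 and Q1008.

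**The stakes are small.** Among 1249 men, 1% to 5% is about 12 to 62 lifetime injectors in both arms together. With 20% attrition, 1249 × 0.8 / 2 ≈ 500 men per arm remain. Ignoring clustering, power to detect a fall from 5% to 2.5% is about 55%: z = 0.025 / √[(0.0475 + 0.0244)/500] = 2.09, and Φ(2.09 − 1.96) ≈ 0.55. From 2.5% to 1.25% it is about 30%. On these assumed rates even a recent-use item would give no reliable arm comparison. This limits the weight of the point. It does not remove the mismatch, or the fact that the item cannot register stopping.

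**Conclusion.** The point holds in a limited form. Section 7.4.1 and Appendix D disagree on how injecting is measured, and that rests on the text alone. If the form is reused as Section 8.2.3 says, Q1009 can detect prevented initiation but not cessation or reduction, and a between-arm odds ratio on it is diluted by men who injected before baseline. The direction follows from the lifetime wording. The size is unknown: the range of 29% to 91% reflects assumed rates and is wide enough to serve only as illustration.

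One item within a secondary endpoint is affected, and probably an uncommon behavior. The marijuana and cocktail items, the primary endpoints and the power statement in Section 9.1.1 are untouched. The repair is cheap and worth making.

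**What to change.** First check the form used at follow-up. If it lacks a recent-injecting item, add one after Q1009 at any remaining wave, in the format of Q1008 and asked only of men who answer yes. State in the protocol that the drug-use endpoint is based on last-12-month items.

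If no wave remains, correct Section 7.4.1 to say that injecting was recorded as lifetime use only, and analyse it solely as new initiation among men who answered no at baseline. That uses answers already collected.

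The cost is one short conditional question put to few men, plus a wording change. An item added late has no baseline value, so it allows a comparison of arms at follow-up without baseline adjustment on the same measure. The initiation analysis says nothing about men who were already injecting, and it would rest on few events if injecting is rare.
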